**2-item Generalized Anxiety Disorder scale**		
	1 of 16. Over the last 2 weeks, how often have you been bothered by *feeling nervous, anxious, or on edge?*	1: Not at all; 2: Several days; 3: More than half the days; 4: Nearly every day; 5: Don’t know; 6: Refuse to answer
	2 of 16. Over the last 2 weeks, how often have you been bothered by *not being able to stop or control worrying?*	1: Not at all; 2: Several days; 3: More than half the days; 4: Nearly every day; 5: Don’t know; 6: Refuse to answer
**8-item Patient Health Questionnaire**		
	3 of 16. Over the last 2 weeks, how often have you been bothered by *little interest or pleasure in doing things?*	1: Not at all; 2: Several days; 3: More than half the days; 4: Nearly every day; 5: Don’t know; 6: Refuse to answer
	4 of 16. Over the last 2 weeks, how often have you been bothered by *feeling down, depressed, or hopeless?*	1: Not at all; 2: Several days; 3: More than half the days; 4: Nearly every day; 5: Don’t know; 6: Refuse to answer
	5 of 16. Over the last 2 weeks, how often have you been bothered by *trouble falling or staying asleep, or sleeping too much?*	1: Not at all; 2: Several days; 3: More than half the days; 4: Nearly every day; 5: Don’t know; 6: Refuse to answer
	6 of 16. Over the last 2 weeks, how often have you been bothered by *feeling tired or having little energy?*	1: Not at all; 2: Several days; 3: More than half the days; 4: Nearly every day; 5: Don’t know; 6: Refuse to answer
	7 of 16. Over the last 2 weeks, how often have you been bothered by *poor appetite or overeating?*	1: Not at all; 2: Several days; 3: More than half the days; 4: Nearly every day; 5: Don’t know; 6: Refuse to answer
	8 of 16. Over the last 2 weeks, how often have you been bothered by *feeling bad about yourself, or that you are a failure, or have let yourself or your family down?*	1: Not at all; 2: Several days; 3: More than half the days; 4: Nearly every day; 5: Don’t know; 6: Refuse to answer
	9 of 16. Over the last 2 weeks, how often have you been bothered by *trouble concentrating on things, such as reading the newspaper or watching television?*	1: Not at all; 2: Several days; 3: More than half the days; 4: Nearly every day; 5: Don’t know; 6: Refuse to answer
	10 of 16. Over the last 2 weeks, how often have you been bothered by *moving or speaking so slowly that other people could have noticed, or the opposite—being so restless that you have been moving around a lot more than usual?*	1: Not at all; 2: Several days; 3: More than half the days; 4: Nearly every day; 5: Don’t know; 6: Refuse to answer
**3-item Sheehan Disability Scale**		
	11 of 16. On a scale from 0-10, to what extent has your health interfered with your *work*, including school work and housework, in the past month (0: Not at all; 10: Extremely)?	Score from 0-10, where 0 means *Not at all* and 10 means *Extremely*
	12 of 16. On a scale from 0-10, to what extent has your health interfered with your *family life* in the past month (0: Not at all; 10: Extremely)?	Score from 0-10, where 0 means *Not at all* and 10 means *Extremely*
	13 of 16. On a scale from 0-10, to what extent has your health interfered with your *social life* or relationships with others outside your family in the past month (0: Not at all; 10: Extremely)?	Score from 0-10, where 0 means *Not at all* and 10 means *Extremely*

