### Design of the Text Messaging Assessment

The SMS text messaging assessment will include 16 questions, delivered in the order of the GAD-2, the PHQ-8, the SDS, and pain assessments (see Table 1). The 16 questions will be sent one at a time. After the participant answers a question by texting back the one number that best describes their feelings, the next message will be sent. The questions are numbered as “1 of 16, 2 of 16...” for participants to track their progress. Since SMS text messaging only supports the delivery of plain text, we use the asterisk sign (ie, *) to highlight the important part of a text message. A sample SMS text messaging assessment question is shown in Figure 1. The SMS text messaging assessment is available in both English and Spanish and implemented using the Qualtrics SMS Distribution module [40].

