**Pain**		
	14 of 16. Have you had pain that has been present most of the time for 6 months or more during the past year?	1: Yes; 2: No; 3: Don’t know
	15 of 16. During the past 4 weeks, how much did pain interfere with your normal work, including both work outside the home and housework?	1: Not at all; 2: A little bit; 3: Moderately; 4: Quite a bit; 5: Extremely; 6: Don’t know
	16 of 16. Please rate your pain by telling us the one number that best describes your pain at its WORST in the last 24 hours (0: No pain; 10: Pain as bad as you can imagine).	Score from 0-10, where 0 means *No pain* and 10 means *Pain as bad as you can imagine*

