### Statistical Analysis

Concordance between SMS text message and interview assessments will be measured by the intraclass correlation coefficient (ICC) and the kappa statistic. ICC measures the consistency or reproducibility of SMS text message and INTW assessments. We will calculate both the consistency and absolute agreement measures of ICC. The kappa statistic measures interrater agreement for categorical items. We will use different threshold levels to compute kappa, including PHQ-2 ≥3 and PHQ-8 ≥8, two threshold levels that were suggested to classify major depression [22,28]. We will also compute paired *t* tests to investigate differences in mean scores between SMS text message and interviewer assessments. ICC and kappa will be computed using the “icc” and “kappa2” functions in the R package “irr” (The R Foundation). Paired *t* tests will be performed by the R function “t.test.” Test-retest reliability of the SMS text message and interviewer assessments will also be measured by ICC. Finally, internal consistency will be measured by Cronbach alpha, which will be computed using the “alpha” function in the R package “psych.”

Since information such as depression and functional disability is sensitive health information, it is critical to understand whether participants are willing to self-disclose such information in an SMS text message assessment. We will calculate the proportion of missing data and explore whether the data are missing at random or is likely to follow some patterns, using descriptive and visualization tools provided by the R packages “mice” and “VIM.” We will also perform multiple imputation on the data and compare the concordance and reliability measures on original and imputed data [47].

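### SMS items 11-16 have no refusal code and each message waits for a reply, so refusal on disability or pain cannot be told from drop-out

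*Protocol article*

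**What the plan says.** All places are in the protocol article.

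- **Response options, Table 1.** Each of the ten GAD-2 and PHQ-8 items (items 1-10) ends with a don't-know code and "6: Refuse to answer". The three Sheehan Disability Scale (SDS) items (11-13) offer only "Score from 0-10, where 0 means *Not at all* and 10 means *Extremely". Item 14 (chronic pain) offers "1: Yes; 2: No; 3: Don’t know". Item 15 (pain interference) offers "1: Not at all; 2: A little bit; 3: Moderately; 4: Quite a bit; 5: Extremely; 6: Don’t know". Item 16 (worst pain) offers only "Score from 0-10, where 0 means *No pain* and 10 means *Pain as bad as you can imagine".
- **Delivery, Methods, Design of the Text Messaging Assessment.** "The 16 questions will be sent one at a time", in the fixed order GAD-2, PHQ-8, SDS, pain. The rule for moving on is: "After the participant answers a question by texting back the one number that best describes their feelings, the next message will be sent".
- **Aim, Methods, Statistical Analysis.** The rationale for the missing-data work is that information such as "depression and functional disability is sensitive health information, it is critical to understand whether participants are willing to self-disclose such information" by SMS. The tools are the proportion of missing data, a descriptive and graphical search for patterns, and multiple imputation with a comparison of original and imputed results.

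**The concern.** The aim and the instrument do not match. The Statistical Analysis section names functional disability as sensitive and asks whether participants will disclose it by SMS. The questionnaire lets participants decline openly on anxiety and depression but not on disability.

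Someone who does not want to answer item 11 has two routes within the flow described. They can text an arbitrary number, which enters the SDS score as if it were genuine. Or they can stop replying, which leaves the same record as fatigue, distraction or a lost phone, and prevents the later items from being sent.

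Two things are at stake. First, for disability and pain, non-response cannot be read as unwillingness to disclose. Second, because order is fixed and each message waits for a reply, the proportion of participants with no reply can only stay level or rise with item position, whatever the content. A plain comparison of missing proportions across scales would mix position with sensitivity.

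**Working it through.** The plan gives no figure on this point, so there is nothing to reproduce. The check is a count from Table 1, the consequence of the sending rule, and two illustrations with assumed rates.

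**1. Codes in Table 1**

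| Items | Scale | Don't know | Refuse |
|---|---|---|---|
| 1-2 | GAD-2 | yes | yes |
| 3-10 | PHQ-8 | yes | yes |
| 11-13 | SDS | no | no |
| 14-15 | Chronic pain, pain interference | yes | no |
| 16 | Worst pain | no | no |

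Ten of 16 items have a refusal code and six do not. Four (11, 12, 13, 16) have neither code.

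**2. Consequence of the sending rule**

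A participant who stops at item k leaves 16 - k items unsent: 5, 4, 3, 2, 1 and 0 for k = 11 to 16. Stopping at any SDS item removes all three pain items.

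**3. Position effect alone**

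The documents give no break-off rate. Assume the same chance r of stopping at every item from item 1, so that sensitivity is equal throughout. The proportion with no reply at item k is 1 - (1 - r)^k. Averages over each scale:

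| r (assumed) | GAD-2 | PHQ-8 | SDS | Pain | SDS / PHQ-8 |
|---|---|---|---|---|---|
| 1% | 1.5% | 6.3% | 11.4% | 14.0% | 1.80 |
| 2% | 3.0% | 12.2% | 21.5% | 26.1% | 1.76 |
| 5% | 7.4% | 27.9% | 45.9% | 53.6% | 1.65 |

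The excess on the SDS comes from its place in the sequence. At r = 2%, 1 - 0.98^10 = 18.3% have already stopped before item 11, so only 21.5 - 18.3 = 3.2 points of the SDS average arise at the SDS items. This table does not measure the effect of the missing codes.

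**4. Loss through refusal by non-reply on items 11-16 only**

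Assume now that everyone reaches item 11, that each of items 11-16 is refused with probability r, and that refusal means no reply. Missingness at item 16 is 1 - (1 - r)^6. With a refusal code that released the next message, item 16 would lose only its own refusals, r. Counts are for the planned group size of 50.

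| r (assumed) | Item 16 missing as written | Of 50 | With a refusal code | Of 50 |
|---|---|---|---|---|
| 1% | 5.9% | 2.9 | 1% | 0.5 |
| 2% | 11.4% | 5.7 | 2% | 1.0 |
| 5% | 26.5% | 13.2 | 5% | 2.5 |
| 10% | 46.9% | 23.4 | 10% | 5.0 |

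If those unwilling to answer items 14-15 send the don't-know code, only items 11, 12, 13 and 16 lose participants. The figure becomes 1 - (1 - r)^4 = 3.9%, 7.8%, 18.5% and 34.4%. These are upper illustrations, since some participants would send an arbitrary number and stay in the sequence.

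**The case against.** The case against is substantial and narrows the point.

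- **The gap would be visible.** A stop at item 11 leaves items 11-16 blank, and the planned pattern exploration would show it. A reader might infer that the loss is hidden, but only its reason goes unrecorded. Neither the exploration nor imputation recovers that reason, and imputation does not touch an arbitrary number, which is not missing.
- **The disclosure question is not lost altogether.** A reader might infer that it cannot be answered for disability. Non-response at each item among those sent it remains observable; only its interpretation as refusal is lost.
- **The missing codes do not produce the scale ratios.** A reader might infer that the SDS would seem to be withheld twice as often as the PHQ-8 because of them. The ratio is 1.65 to 1.80 at the assumed rates, and it reflects break-off from item 1, which new codes on items 11-16 would not cure. Nor does the plan commit to comparing raw proportions between scales.
- **Loss of later items is not universal.** The don't-know code releases the next message at items 14-15, and nothing follows item 16.
- **Handling of invalid replies, timeouts and reminders is not described** in the article and may stand in the full protocol. The response options and the sending rule, however, are fixed here.
- **Bias from arbitrary numbers** in the SDS scores or their concordance is possible, but the documents support neither a size nor a direction.
- **Reach is limited.** The GAD-2 and PHQ-8 come first and have refusal codes, and the kappa thresholds named are on the PHQ-2 and PHQ-8.

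What remains is the mismatch between the SDS options and an aim that names functional disability.

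**Conclusion.** The point holds as a cheap improvement. On items 11-16, and most clearly on SDS items 11-13, the SMS instrument as described cannot separate refusal from drop-out or from an arbitrary answer, although disclosure of functional disability is a stated question. This follows from Table 1 and the sending rule and needs no assumption about rates.

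Separately, the no-reply proportion cannot fall with item position. The 1.65- to 1.80-fold SDS excess rests on assumed break-off of 1% to 5% per item, constant and independent of content. The item 16 losses in step 4 rest on assumed refusal rates of 1% to 10% and refusal by silence. No rate is given in the documents, so these figures show direction and possible scale, not an estimate for this study.

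The missing codes do not affect the recording of depression or anxiety refusals.

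**What to change.** **Instrument, for any further use.** Add non-scored don't-know and refusal codes outside 0-10 to items 11-13 and 16, and a refusal code to items 14-15. Use the same codes in both modes and let each release the next message. Scoring is unchanged; the cost is a wording change to six messages and slightly longer texts.

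**Analysis, for data already collected.** The Results section reports that enrolment ran from June to November 2017, so this part is the usable one for this study.

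1. Report SMS non-response at item k among participants who were sent item k, in place of the raw missing proportion. Show coded refusals and don't-knows separately from no reply.
2. State that on items 11-16 refusal cannot be separated from drop-out, and that the self-disclosure conclusion for disability and pain is therefore limited to non-response.

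This costs one table and a sentence of limitation, and needs no new data.

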**Pain**		
	14 of 16. Have you had pain that has been present most of the time for 6 months or more during the past year?	1: Yes; 2: No; 3: Don’t know
	15 of 16. During the past 4 weeks, how much did pain interfere with your normal work, including both work outside the home and housework?	1: Not at all; 2: A little bit; 3: Moderately; 4: Quite a bit; 5: Extremely; 6: Don’t know
	16 of 16. Please rate your pain by telling us the one number that best describes your pain at its WORST in the last 24 hours (0: No pain; 10: Pain as bad as you can imagine).	Score from 0-10, where 0 means *No pain* and 10 means *Pain as bad as you can imagine*

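### Reply digits in Table 1 change meaning between items, most clearly at item 14, so SMS keying slips on the pain and SDS items could pass unnoticed

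*Protocol article*

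**What the plan says.** Methods, Design of the Text Messaging Assessment: 16 questions go out singly, in the order GAD-2, PHQ-8, SDS, pain. Each is answered by "texting back the one number that best describes their feelings", and the next message follows the reply.

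Table 1 gives the reply keys:

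- Items 1-10 (GAD-2 and PHQ-8): "1: Not at all; 2: Several days; 3: More than half the days; 4: Nearly every day; 5: Don’t know; 6: Refuse to answer".
- Items 11-13 (SDS): "Score from 0-10, where 0 means *Not at all* and 10 means *Extremely".
- Item 14 (chronic pain): "1: Yes; 2: No; 3: Don’t know".
- Item 15 (pain interference): "1: Not at all; 2: A little bit; 3: Moderately; 4: Quite a bit; 5: Extremely; 6: Don’t know".
- Item 16 (worst pain): a 0-10 score with 0 as no pain.

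Overall Design makes SMS-interviewer concordance for functional disability and pain part of the objective, and lists the presence of chronic pain as a measure. Statistical Analysis plans ICC, kappa for categorical items and paired t tests on mean scores. It also looks at missing data to learn whether participants are willing to disclose by SMS.

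**The concern.** A participant without symptoms has to text '1' ten times, then 0, 0, 0, then 2, then 1, then 0. Someone who goes on texting '1' is recorded with an SDS total of 3 out of 30, chronic pain present and worst pain 1 out of 10. Each of those replies is valid, so a range check would not catch them.

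The non-response codes have the same weakness. A participant who refuses items 1-10 with '6' and continues with '6' is scored 3 × 6 = 18 out of 30 on the SDS, not missing. With '5' (don't know) the total is 3 × 5 = 15.

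An interviewer can hear hesitation and clarify an answer, whereas SMS delivers only the digit. Slips of this kind are therefore likely to be more common in one of the two modes being compared. They could be taken for a real mode difference in pain or disability, or could hide refusals from the missing-data analysis.

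**Working it through.** **Step 1. Item count.** 2 (GAD-2) + 8 (PHQ-8) + 3 (SDS) + 3 (pain) = 16, as stated.

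**Step 2. Keys side by side (Table 1).**

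| Items | Symptom-free reply | What '1' records | Don't know | Refuse |
|---|---|---|---|---|
| 1-10 | 1 | no symptom | 5 | 6 |
| 11-13 | 0 | 1 out of 10 | none listed | none listed |
| 14 | 2 | chronic pain present | 3 | none listed |
| 15 | 1 | no interference | 6 | none listed |
| 16 | 0 | 1 out of 10 | none listed | none listed |

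So '1' is the no-symptom reply on 11 items, one step above none on 4 and a positive answer on 1 (11 + 4 + 1 = 16). Every digit from 1 to 6 used on items 1-10 is a valid SDS score. On item 14 only 1, 2 and 3 are valid: a carried-over '1' records Yes, '2' records No and '3' records don't know, while 4 to 6 fall outside the key.

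**Step 3. Effect on kappa for item 14.** The documents give no prevalence, agreement or slip rate, so all three are assumed. Take prevalence p in both modes, underlying kappa 0.80 and symmetric disagreement. Then kappa = (po − pe)/(1 − pe), with po the observed and pe the chance agreement.

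At p = 0.40:

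- pe = 0.16 + 0.36 = 0.52 and po = 0.52 + 0.80 × 0.48 = 0.904.
- Each discordant cell is 0.048, both-Yes is 0.352 and both-No is 0.552.

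Move a fraction f of both-No to SMS Yes (carried-over '1'):

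- f = 5%: po = 0.904 − 0.0276 = 0.8764, SMS Yes = 0.4276, pe = 0.5145, kappa = 0.745.
- f = 10%: po = 0.8488, SMS Yes = 0.4552, pe = 0.5090, kappa = 0.692.

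At p = 0.30 the same steps give 0.730 and 0.664.

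Starting instead from perfect agreement, f = 5% and 10% give 0.938 and 0.878 at p = 0.40, and 0.884 and 0.783 at p = 0.20.

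**Step 4. The opposite slip.** Move f of both-Yes to SMS No (carried-over '2'), at p = 0.40 and underlying kappa 0.80:

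- f = 5%: po = 0.904 − 0.0176 = 0.8864, SMS Yes = 0.3824, pe = 0.5235, kappa = 0.762.
- f = 10%: po = 0.8688, SMS Yes = 0.3648, pe = 0.5270, kappa = 0.723.

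Kappa falls in both cases, but SMS prevalence rises in Step 3 and falls here.

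**Step 5. SDS total.** If a share q is truly 0 on each item and a fraction f of them text '1', the mean shift is 3 × q × f. For q = 0.30-0.60 and f = 2%-20% this runs from 3 × 0.30 × 0.02 = 0.02 to 3 × 0.60 × 0.20 = 0.36 points on a 0-30 scale. No one person moves by more than 3 points through carried-over '1's. The cross-mode groups hold 52 + 49 = 101 participants, so the standard error of a paired mean difference is SD/√101 if all pairs are complete. The SD is not in the documents: 2.5-2.9 would give 0.25-0.29, and 5 would give 0.50.

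**Step 6. Depression and anxiety scores.** On items 1-10 '1' always means no symptom, and these items come first. The shift from carried-over '1's is 0, and the two named kappa thresholds (PHQ-2 ≥3, PHQ-8 ≥8) are unaffected.

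**The case against.** Mixed response formats are normal when different instruments are joined, and Table 1 gives each item its own options. Items arrive one at a time. Each SDS message also restates its anchors ("in the past month (0: Not at all; 10: Extremely"), so three labelled 0-10 items stand between the run of '1's and item 14. A symptom-free participant who answers 0, 0, 0 has no '1' left to carry over. This stands as a reason to expect few slips. It does not exclude them, because the SDS items also accept '1'.

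A reader might infer that habitual texters do record symptoms they lack, only by SMS and always towards more pain and disability. The documents do not support that:

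- They report no keying errors.
- Direction is open, as Step 4 shows. A habitual '4' carried into the SDS could understate disability.
- Randomization and Data Collection Plan says only that the interviewer repeats the same assessment. Whether telephone answers are words or digits is not described, so a smaller error by telephone is plausible but inferred.

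The remedy can also be challenged. Recruitment ended in November 2017, so re-keying cannot help this study. With 0 as absence throughout, a habitual '0' could become a false negative, and a '1' carried into item 14 would still record Yes. Re-keying therefore reduces the problem without removing it.

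**Conclusion.** The inconsistency is certain from Table 1; its effect is a possibility of unknown frequency and unknown net direction. It is confined to the related conditions: chronic pain, where item 14 is the one full reversal, and to a small degree the SDS. Under the assumptions in Step 3, slip rates of 5%-10% cost roughly 0.05-0.14 of kappa on item 14 (0.80 to between 0.75 and 0.66). A carried-over '1' shifts the SDS mean by at most a few tenths of a point at slip rates up to 20%. Carried-over non-response codes could move an individual SDS total much further, but the documents give no rate for them either.

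One might go further and predict that SMS will look reliable on retest yet discordant with the interviewer. That would need the same slip on both SMS occasions; slips that are not repeated would lower SMS/SMS reliability instead. The point is a cheap improvement and does not threaten the depression results.

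**What to change.** **For any reuse of the instrument, in both modes:** key items 1-10 as 0-3, item 14 as 0 = No and 1 = Yes, and item 15 as 0-4, leaving the SDS and item 16 as they are. Use one don't-know/refuse code that is never a valid score. A number outside 0-10 would keep the one-number reply format.

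**For replies collected with the printed keys:**

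- Flag assessments in which one digit continues from items 1-10 through items 11-14, and those in which 5 or 6 runs on into the SDS.
- Check item 14 against items 15 and 16.
- Report the number flagged by mode, which also tests whether slips are commoner by SMS.
- Give SDS and chronic-pain agreement with and without flagged assessments, as a sensitivity analysis.

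**Cost:** a little extra analysis and alignment of the interviewer form with the new keys. The flag will catch some genuine responders and miss some slips, so the unflagged-only result should stand beside the full result, not replace it.
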